## Funding and research agreement

This is an investigator-driven study which is fully funded by a Swedish Research Council grant, grant number 2020-00301. The sponsor and site PIs agree to fulfil their respective duties within the study as detailed in the Site Agreement. The sponsor has full access to, and retains all rights to, the data generated in the study. The site PIs participate as co-authors in the publication of the primary endpoint (expected highest impact publication) and may also participate in additional publications based on interest and contribution, as agreed. The Sites will also receive reimbursement for included and fully investigated (including month 3 data collection) study participants as detailed in the Site Agreement.

## List of used acronyms and abbreviations

| Abbreviation | Term/Explanation                                                                                                                                              |
|--------------|---------------------------------------------------------------------------------------------------------------------------------------------------------------|
| ADE          | Adverse Device Effect                                                                                                                                         |
| AE           | Adverse Event                                                                                                                                                 |
| CIP          | Clinical Investigational Plan                                                                                                                                 |
| CRF          | Case Report Form                                                                                                                                              |
| DD           | Device Deficiency                                                                                                                                             |
| DHI          | Dizziness Handicap Inventory                                                                                                                                  |
| GCP          | Good Clinical Practice                                                                                                                                        |
| IB           | Investigator's Brochure                                                                                                                                       |
| ICMJE        | International Committee of Medical Journal Editors                                                                                                            |
| IFU          | Instructions for Use                                                                                                                                          |
| ISO          | International Organization for Standardization                                                                                                                |
| ITT          | Intention-to-treat = including all data from all subjects who have participated in the study                                                                  |
| LVFS         | Läkemedelsverkets författningssamling (English: Swedish Medical Products Agency's statutes)                                                                   |
| PP           | Per Protocol analysis = including only data from subjects who have completed the study completely in accordance with the CIP, with no deviations from the CIP |

|        |                                             |
|--------|---------------------------------------------|
| SADE   | Serious Adverse Device Effect               |
| SAE    | Serious Adverse Event                       |
| USADE  | Unanticipated Serious Adverse Device Effect |
| VSS-SF | Vestibular Symptom Scale – Short Form       |
| vHIT   | Video Head Impulse Test                     |
| VOR    | Vestibulo-ocular reflex                     |

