| Compare the effect of online vestibular rehabilitation with standard written instructions after acute onset vertigo on vestibular symptoms (superiority).                                                                                                                                                                                                                                                                                                                                                                                                                                                                                                                                                                                                                                                                                                                                                                                                                                                                                                                                                                                                                                                                                                                                   | The vertigo symptom scale short form (VSS-SF) score at 6 weeks after vertigo onset.                                                                                                                                                                                                                                                                                                                                                                                                                                                                                                                                                                                                                                                                                                                                                                                                                                                                                                                                                                                                                                                                                                                                                 |

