#### 6.4. End of the clinical investigation

The clinical investigation ends when the last subject has completed the last follow-up. The sponsor will notify the Swedish Medical Products Agency within 15 days after the end of the clinical investigation.

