### 6.7. Procedures

**Figure 1. Study outline – Internet-based vestibular rehabilitation versus standard care after acute onset vertigo, a randomized controlled trial**

[figure not shown]

VSS-SF – vertigo symptom scale short form. vHIT – video head impulse test. EQ-5D – EuroQol five-dimension scale. DHI – dizziness handicap inventory. T25-FW – timed 25-foot walk test. BPPV – benign paroxysmal positional vertigo. q – questions, t – testing.

Eligible patients will be identified by the site study coordinator using daily emergency department, medical/neurological and ENT wards vigilance (contacting the on-call doctors, contacting the emergency department staff, manual patient list screening including screening of the relevant wards, notice-board ads and information brochures at each department and ward). ENT outpatient clinics identify eligible patients from subacute AVS visits. Local variations of these methods to identify eligible patients will be put in place by each site PI. Eligible patients are screened for participation with a screening checklist (inclusion/exclusion criteria) including screening for nystagmus using videofrenzel goggles (screening of eye movements looking straight forward, 30 degrees to the right, 30 degrees to the left, up, and down); the presence of nystagmus must be documented to be present at least 24 hours after symptom debut.

Subjects will be randomized to the intervention group or control group as detailed in section 6.2.

**Intervention:** Online 6 weeks vestibular rehabilitation demanding 15–20 minutes of training each day. The intervention aims at maximizing central compensation for the vestibular/balance deficit. It consists of weekly online sessions and daily exercises. The

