weekly online sessions consist of educational texts, symptom control techniques, scoring tests and exercise prescriptions for the following week. The exercises for the following week after each online session will be adapted to the user and thus become successively more difficult if the user scores lower discomfort during evaluations, or the opposite if the user scores higher discomfort. There are 6 different exercises in the tool: 1. Head shake with open eyes, gaze following the head; 2. Head nod with open eyes, gaze following the head; 3. Head shake with closed eyes; 4. Head nod with closed eyes; 5. Head shake with open eyes, gaze fixated and; 6. Head nod with open eyes, gaze fixated. These exercises are performed sitting, standing and walking depending on symptom intensity. There are 4 symptom control techniques in the tool in order to deal with secondary anxiety issues related to the vertigo: 1. Controlled breathing; 2. Relaxation; 3. Stress management and; 4. Thought control.

Control: After randomization written instructions with the 6 different exercises from the online rehabilitation tool is handed out and the participant is instructed to increase difficulty if possible. Participants are also given general advice to prevent inactivity and secondary dizziness and fear of motion. Data collection as for the intervention arm. At the end of the core study at 3 months from randomization the standard care study arm participants will also be granted access to the online rehabilitation tool and followed until 12 months.

The Swedish translations of VSS-SF, DHI, and EQ-5D-3L are collected locally at all sites by the site study coordinator. These questionnaire data will be collected by in-person interview at day 0, week 6 and after 3 months, except for VSS-SF at 6 weeks (primary endpoint) which will be collected by phone call interview by a blinded study coordinator at either the same site or a different site. In the case of the first 100 included subjects, the VSS-SF at 6 weeks (primary endpoint) will be collected by phone call interview twice, 48 hours apart, as part of the statistical validation of the Swedish translation of the VSS-SF questionnaire. Also, at week 3 and after 12 months VSS-SF and EQ-5D data will be collected by phone call interview (figure 1).

The T25-FW data will be collected by letting the subject walk a clearly marked 25-foot course during follow-up appointments at each site.

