## 9. Statistical considerations

### 9.1. Analysis population

The primary analysis will be performed using the intention to treat cohort on both primary and secondary outcomes. Per protocol analyses will also be performed as part of the sensitivity analysis.

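### The per-protocol set requires the whole study to be completed with no deviation of any kind, so events after week 6 would remove valid week-6 primary-endpoint scores from the sensitivity analysis

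*Protocol*

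**What the plan says.** The list of abbreviations defines a per-protocol analysis as "including only data from subjects who have completed the study completely in accordance with the CIP, with no deviations from the CIP". No other definition appears. Section 9.1 makes intention to treat the primary analysis and adds: "Per protocol analyses will also be performed as part of the sensitivity analysis". It does not redefine the set, grade deviations or set a time limit. Section 12 requires every deviation to be documented and reported, also without grading.

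The primary endpoint in section 5.2 is "The vertigo symptom scale short form (VSS-SF) score at 6 weeks after vertigo onset". By section 6.7 it is collected in a telephone interview by a blinded coordinator. Table 1 then schedules a month-3 visit (day 90 ± 7) and a 12-month call (day 360 ± 14). Section 6.4 states: "The clinical investigation ends when the last subject has completed the last follow-up". Section 6.7 says that, at the close of the 3-month core study, "the standard care study arm participants will also be granted access to the online rehabilitation tool and followed until 12 months".

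**The concern.** A per-protocol analysis of a week-6 outcome should ask whether the comparison up to week 6 was carried out as planned. What happens at month 3 or month 12 cannot answer that. Under the stated rule, a participant who was eligible, received the allocated material and gave a valid blinded score at week 6 is still excluded if the 12-month call takes place on day 375.

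The loss need not be random. Whether someone keeps later appointments may depend on how well they have recovered. After month 3 it may also depend on arm, because only controls are newly given the tool then. The remaining set is therefore conditioned on events that follow the outcome and may be related to both outcome and arm. In a trial that section 3.3 calls pivotal and confirmatory, agreement between such a set and intention to treat would give little reassurance, and disagreement would be hard to interpret.

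**Working it through.** **Does the rule reach past week 6?** There are two readings of when a participant has completed the study.

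- *Full follow-up (sections 6.4 and 6.7, Table 1).* Two contacts follow week 6. The permitted days are 90 ± 7 = 83 to 97 and 360 ± 14 = 346 to 374, so a call on day 375 is out of window. The last target day is 360 − 42 = 318 days after the week-6 target.
- *3-month core study (section 6.7).* One contact, the month-3 visit, still follows week 6.

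The rule reaches past the primary endpoint on either reading.

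**Planned number with week-6 data.** Section 9.4 gives 156 evaluable participants (78 per arm) and 184 after 15% drop-out. The inflation step reproduces: 156 / (1 − 0.15) = 183.5, rounded up to 184. The 156 itself does not reproduce if 0.6 is read as a correlation (the exact ANCOVA calculation gives 246); it does if 0.6 is read as R². That is a separate matter. Here 156 serves only as the planned denominator.

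**Size of the loss.** The protocol gives no deviation rate. Let q be the assumed chance of a disqualifying deviation at each contact after week 6, independent between contacts.

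Full follow-up: kept = 156 × (1 − q)².

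| q | Kept | Week-6 values discarded |
|---|---|---|
| 2% | 156 × 0.9604 = 150 | 6 |
| 5% | 156 × 0.9025 = 141 | 15 |
| 10% | 156 × 0.81 = 126 | 30 |
| 15% | 156 × 0.7225 = 113 | 43 |
| 20% | 156 × 0.64 = 100 | 56 |

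Core study only: discarded = 156 × q, which is about 8, 16 and 31 at q = 5%, 10% and 20%.

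These counts cover later contacts only. Trivial deviations elsewhere would add to them by an amount that the protocol does not allow one to estimate. A set restricted to events up to week 6 would lose none of these values.

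**The case against.** **It is only a sensitivity analysis.** This stands. Intention to treat is primary in section 9.1, and the pass criterion in section 9.5 does not mention the per-protocol set. Sections 9.9 and 9.10 plan other sensitivity analyses, so this set is not the only robustness check.

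**It is a glossary entry, and detail belongs in the statistical analysis plan.** This stands only in part. Grading of deviations is commonly settled there, and its absence alone would be no finding. But the protocol does state a rule, and that rule does not suit a week-6 endpoint. Section 9.11 makes the analysis plan outlined in the protocol the reference from which relevant departures are reported to the agency, so a different set defined later would conflict with the text.

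**A stronger reading: the rule is unequal between arms.** The intervention is described as "Online 6 weeks vestibular rehabilitation demanding 15–20 minutes of training each day", whereas for controls "written instructions with the 6 different exercises from the online rehabilitation tool is handed out and the participant is instructed to increase difficulty if possible", with no daily amount given. A reader might infer that each missed training day is a deviation in one arm only, so that the set would keep just the most persistent intervention participants. The documents do not support this:

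- No section calls a missed training day a deviation. Section 12 concerns what investigators may not do, and section 6.6.3 keeps participants who can no longer train in the study for data collection.
- Table 1 records compliance as weekly sessions at weeks 3 and 6. It schedules no daily log from which a 42-of-42-days rule could be applied.
- The control leaflet is not shown, and section 8.3 indicates that controls receive instructions beyond those described in section 6.7.
- Section 9.10 already plans an adherence analysis that treats both arms alike: it drops the lowest 10% by self-reported weekly sessions in each.

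**A larger loss.** If 90% of participants met each of the four follow-up windows, 184 × 0.90⁴ × 0.85 gives about 103 remaining. A reader might quote this as the damage done by later events. It is not, because it includes the day-21 and day-42 windows and the planned attrition.

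**Conclusion.** The point holds in limited form. The stated definition, applied as section 9.1 commits to apply it, discards valid blinded week-6 scores because of events after week 6 or trivial deviations. This follows from the text and does not depend on whether the study is taken to end at 3 or 12 months.

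The size is illustrative. With assumed independent rates of 5%, 10% or 20% at each of two later contacts, about 15, 30 or 56 of 156 values are lost. The direction of any resulting bias cannot be told from the documents, and nothing shows that retention after week 6 will in fact differ by recovery or arm. The primary intention-to-treat result is not affected. The change is worth making because it is cheap and the present set would be hard to interpret.

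**What to change.** Replace the abbreviation-list entry, or override it in section 9.1, as follows:

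- For the week-6 VSS-SF, determine per-protocol membership only from information up to and including week 6.
- Exclude only for major deviations that affect eligibility, the allocated treatment or the primary assessment. Fix the list, and classify deviations against it, before the statistical analysis is unblinded.
- State that contacts missed or out of window after week 6 do not remove anyone from the week-6 analysis.
- If adherence is to be part of the definition, apply one criterion to both arms, based on the self-reported weekly sessions already used in section 9.10. State that single missed training days are not deviations, which closes off the unequal reading.

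The cost is one reworded definition and one blinded classification of deviations that are already being recorded. No new data are needed. The small downside is a less strict set.

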## 1. Synopsis

|                           |                                                                                                                                                                                                                                                                                                                                                                                                                                                                                                                                                                                                                                                                                                                                                |
|---------------------------|------------------------------------------------------------------------------------------------------------------------------------------------------------------------------------------------------------------------------------------------------------------------------------------------------------------------------------------------------------------------------------------------------------------------------------------------------------------------------------------------------------------------------------------------------------------------------------------------------------------------------------------------------------------------------------------------------------------------------------------------|
| Background and rationale: | Acute onset vertigo is common and entails much suffering with persisting symptoms at 3 months after onset in up to half of those afflicted. Vestibular rehabilitation to aid recovery is not readily available. The purpose of this study is to investigate the effects on vertigo symptoms of a 6-week online vestibular rehabilitation tool compared with standard care (written instructions leaflet) after acute onset vertigo.                                                                                                                                                                                                                                                                                                            |
| Investigational device:   | Online vestibular rehabilitation tool                                                                                                                                                                                                                                                                                                                                                                                                                                                                                                                                                                                                                                                                                                          |
| Number of subjects:       | 184                                                                                                                                                                                                                                                                                                                                                                                                                                                                                                                                                                                                                                                                                                                                            |
| Inclusion criteria (all): | 
 
• <math>\geq 18</math> years old; and
 
• The subject has given written consent to participate in the study; and
 
• New acute onset dizziness or vertigo since <math>\geq 24</math> hours with pathological spontaneous or gaze-evoked nystagmus (i.e., an acute vestibular syndrome, AVS). The nystagmus as described above must be present at investigation between 24 hours and 7 days from onset, spontaneously, gaze-evoked or head-shake evoked and documented; and
 
• Screening and inclusion within 7 days of onset of continuous symptoms; and
 
• Symptomatic at inclusion
 
                                               |
| Exclusion criteria (any): | 
 
• Pre-existing vestibular disease or neurological disease anticipated to affect the ability to participate in the study or the effect of the intervention. N.B: Recurring AVS with no set diagnosis before inclusion is accepted, as is past transient neurological diseases such as TIA or migraine; or
 
• Inability to use the online rehabilitation tool, e.g., due to not having access to a computer, tablet or smartphone, not having access to the internet or lacking in experience with such tools; or
 
• Mental inability, reluctance or language difficulties that result in difficulty understanding the meaning of study participation; or
 
 |

|                   |                                                                                                                                                                                                                                                                                                                                                                                                                                                                                                                                                                                                                                                                                                                                                                                                                                                                                                                                                                                                                                                                                                                                                                                                                                                                                                                                                                                                                                 |
|-------------------|---------------------------------------------------------------------------------------------------------------------------------------------------------------------------------------------------------------------------------------------------------------------------------------------------------------------------------------------------------------------------------------------------------------------------------------------------------------------------------------------------------------------------------------------------------------------------------------------------------------------------------------------------------------------------------------------------------------------------------------------------------------------------------------------------------------------------------------------------------------------------------------------------------------------------------------------------------------------------------------------------------------------------------------------------------------------------------------------------------------------------------------------------------------------------------------------------------------------------------------------------------------------------------------------------------------------------------------------------------------------------------------------------------------------------------|
|                   | 

• Medical and/or physical contraindications to making the required head movements (e.g., vertebral dissection) or otherwise participating in the training and testing exercises or data collection; or

• Medication or other substance intake which can affect the ability to participate in the study or the reliability of the measurement methods. These medications include regular use of: Anticonvulsants, antiemetics/motion sickness medications, benzodiazepines, neuroleptics. Transient corticosteroid and/or antiemetic treatment related to the current vertigo is accepted.

                                                                                                                                                                                                                                                                                                                                                                                                                                                                                                                                                                                                                                                                                                                                                                        |
| Study objectives: | 
Primary objective:
To compare the effect of the online vestibular rehabilitation tool with standard written instructions after acute onset vertigo on vestibular symptoms.
 
Secondary objectives:
 

1. Compare the impact of the online vestibular rehabilitation tool with standard written instructions after acute onset vertigo on different aspects of everyday living.

2. Compare how the online vestibular rehabilitation tool influences the walking ability compared with standard written instructions after acute onset vertigo.

3. Compare how the online vestibular rehabilitation tool influences the lateral canal vestibulo-ocular reflex (VOR) recovery compared with standard written instructions after acute onset vertigo.

4. Compare the long-term effects of early vs. delayed online vestibular rehabilitation on vestibular symptoms and mobility.

5. Compare the effects of online vestibular rehabilitation with standard written instructions on vestibular rehabilitation compliance.

6. Compare the health economic effects of online vestibular rehabilitation with standard written instructions.

7. Compare the multi-joint kinematic output data from a portable multi-sensor movement analysis system, with the hip kinematic output data received from the mobile phone app.

 |

|                  |                                                                                                                                                                                                                                                                                                                                                                                                                                                                                                                                                                                                                                                                                                                                                                                                                                                                                                                                                                                                                                                                                                                                                                                                                                                            |
|------------------|------------------------------------------------------------------------------------------------------------------------------------------------------------------------------------------------------------------------------------------------------------------------------------------------------------------------------------------------------------------------------------------------------------------------------------------------------------------------------------------------------------------------------------------------------------------------------------------------------------------------------------------------------------------------------------------------------------------------------------------------------------------------------------------------------------------------------------------------------------------------------------------------------------------------------------------------------------------------------------------------------------------------------------------------------------------------------------------------------------------------------------------------------------------------------------------------------------------------------------------------------------|
|                  | 
8. Translate and validate the VSS-SF scale from English to Swedish.
 
9. Investigate the frequency of benign positional paroxysmal vertigo (BPPV) after AVS at different time points and using different evaluation methods; investigate the correlation between BPPV the DHI, VSS-SF, steps and safety endpoints; and investigate the effect of treatment arm allocation on the risk for BPPV.
 
Safety objective(s): Compare the effects on the risk of falls/fractures of online vestibular rehabilitation compared with standard written instructions.
                                                                                                                                                                                                                                                                                                                                                                                                                                                                                                                                                                                                                                                                                |
| Study endpoints: | 
Primary endpoint:
The vertigo symptom scale short form (VSS-SF) score at 6 weeks after vertigo onset.
 
Secondary endpoints:
 
1. The between groups mean dizziness handicap inventory (DHI) score at 6 weeks and 3 months after vertigo onset.
 
2a. The between groups changes in timed 25-foot walk test (time duration; T25-FW) from baseline to 6 weeks and 3 months; the between group changes in kinematic and temporal parameters during walking (body sway, range of motion, gait phase durations) at 6 weeks and 3 months after vertigo onset.
 
2b. The between groups changes in body sway during the Romberg test, from baseline to 6 weeks and 3 months after vertigo onset.
 
3. The between groups changes in video head impulse test (vHIT, site-dependent) measured lateral canal VOR gain and saccades from baseline at 6 weeks and 3 months after vertigo onset.
 
4. The between groups mean vertigo symptom scale short form (VSS-SF) score at 12 months after vertigo onset; and the between group pedometer-derived number of steps walked since last visit at 6 weeks and 3 months after vertigo onset.
 
5. The between groups mean number of weekly training sessions at 6 weeks.
 |

|                                                 |                                                                                                                                                                                                                                                                                                                                                                                                                                                                                                                                                                                                                                                                                                                                                                                                                                                                                                                                                                                                                                                                                         |
|-------------------------------------------------|-----------------------------------------------------------------------------------------------------------------------------------------------------------------------------------------------------------------------------------------------------------------------------------------------------------------------------------------------------------------------------------------------------------------------------------------------------------------------------------------------------------------------------------------------------------------------------------------------------------------------------------------------------------------------------------------------------------------------------------------------------------------------------------------------------------------------------------------------------------------------------------------------------------------------------------------------------------------------------------------------------------------------------------------------------------------------------------------|
|                                                 | 
6. Register-based search for health economic effects on all levels of care (primary, specialized) and society (sick leave).
 
7. The difference in kinematic output between measurement systems (i.e., multi-sensor and mobile app) during the tests specified in 2a and 2b.
 
8. The reliability and validity of the Swedish VSS-SF translation.
 
9. The frequency (percentage) of participants with:
BPPV at 3 months after AVS onset;
symptoms indicating BPPV 6 weeks after an AVS using a BPPV specific questionnaire;
positional nystagmus (non-BPPV) 3 months after an AVS;
positional vertigo (non-BPPV) 3 months after an AVS;
BPPV in the treatment vs control group; and
the DHI/VSS-SF/steps/safety results differences between the BPPV, suspected BPPV and non-BPPV groups.
 
Safety endpoint:
The proportion of participants who has experienced falls/fractures since study start up until 6 weeks, 3 months and 12 months; and the number of falls/fractures in each study arm at the same time points.
 |
| Planned duration of the clinical investigation: | October 2021 –December 2024                                                                                                                                                                                                                                                                                                                                                                                                                                                                                                                                                                                                                                                                                                                                                                                                                                                                                                                                                                                                                                                             |

